##### Other study outcomes

Differences in costs and QALYs between enhanced therapy and usual care will be assessed using independent samples *T*-tests, with 95% bias-corrected and accelerated confidence intervals around the mean difference to account for sampling variability, stratified for a maximum of two variables that are univariately associated with the outcome. For cost-effectiveness, the approach will be identical to the approach for cost-utility described above, with foot ulcer recurrence as the clinical outcome. For all other study parameters (see the “Outcomes {12}” section), differences between enhanced therapy and usual care will be assessed via independent sample* T*-tests (for normally distributed data) or Mann–Whitney *U*-tests (for not normally distributed data) in case of interval or ratio data, and with chi-square or Fisher’s exact tests in case of nominal or ordinal data.

In addition, a budget impact analysis (BIA) will be done. The budget impact analysis will be carried out from governmental, health care provider, and insurer perspectives. The governmental perspective is chosen to help setting priorities in health care optimization while simultaneously considering the wider implications of stimulating enhanced therapy for diabetic patients at a high risk of ulcers beyond the health care sector. The provider perspective is chosen to support local decisions on economies of scale and affordability. The insurer perspective is chosen to assess the net financial consequences of offering intensified monitoring to high-risk patients who already have had ulcers in the past, which may help to shift health care use from the second to the first echelon. The BIA will be conducted using a decision-tree model developed in Microsoft® Excel. The BIA will be performed according to the Professional Society for Health Economics and Outcomes Research Task Force principles. We will use multiple scenarios with different numbers for the population to target, different treatment adherence, and different implementation scenarios, based on the best estimates available at the time of analysis.

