### Trial design {8}

The study design is a multicenter, parallel-group, superiority RCT with two study arms with a 1:1 allocation ratio:Enhanced therapy, which includes usual care as provided in the Netherlands and, in addition, an integrated personalized assistive devices approachUsual care as provided in the Netherlands

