For cost-utility as primary health-economic outcome measure, we anticipate a clinically relevant 0.1 gain in QALYs for the enhanced therapy group with group standard deviations for QALYs of 0.15 [64]. We use an estimation of cost difference of €0 per participant between both groups with group standard deviations for costs of €1000 [65, 66]. We allow room here for a more positive outcome in costs, as we predict an average cost saving per participant of €1113.75 for enhanced therapy based on the expected clinical effect of 59% relative reduction in number of ulcers compared with usual care (see Table 1). With a willingness to pay (WTP) of €50,000, a correlation between costs and QALYs (*ρ*) of 0, *α* = 0.05 (two-sided), power = 80%, and a drop-out rate of 20%, this leads to a sample size of 63 participants per study group, or 126 participants in total. Without drop-out, a sample size of (63 × 0.8 =) 51 participants per study group or 102 in total is required.

**Table 1 Tab1:** Average predicted costs per participant

				**Enhanced therapy**		**Usual care**	
**Modality**	**Event/activity**	**Time (hours)**	**Unit costs**	**Expected frequency**	**Expected costs**	**Expected frequency**	**Expected costs**
	Ulcer development [6]	-	€10,000	0.15	€1500	0.37	€3700
	Podiatrist	1	€100	0.50	€50	0.00	€0
Custom-made footwear	Optimization equipment: pressure measurements [36]	-	€50	1.00	€50	0.00	€0
	Shoe technician	1	€100	2.00	€200	0.00	€0
Custom-made indoor footwear	Production and optimization [13]	-	€400	0.95	€380	0.00	€0
Personalized temperature monitoring	Thermometry [38]	-	€75	0.75	€56.25	0.00	€0
Personalized education	Structured education	1	€100	0.50	€50	0.00	€0
	Motivational Interviewing	1	€100	2.00	€200	0.00	€0
	Equipment [49, 57]	-	€100	1.00	€100	0.00	€0
**Total**					€2,586.25		€3,700

Average of predicted additional costs per participant of enhanced therapy versus usual care, based on the expected frequencies as described in the power calculation. For all costs except ulcer development, usual care is used as index. Unit cost estimations are based on previous studies and standard hourly wages of a college educated professional in the Netherlands

With the power calculations showing a requirement of 122 participants for the primary clinical outcome, 120 for the primary patient-related outcome, and 126 for the primary health-economic outcome, a sample size of 126 participants provides adequate power for all three primary outcomes.

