### Statistical methods

#### Statistical methods for primary and secondary outcomes {20a}

Statistical analysis will be performed after the last follow-up visit of the last participant using SPSS statistical software (IBM Corporation, Armonk, NY). All tests will assess group effects, will be two-sided, and use *P* < 0.05 as significance level. All comparisons between groups are based on both intention-to-treat and final visit end-point analysis.

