##### Primary study outcomes

For each of the three specified outcomes related to proportion of participants with a recurrent foot ulcer (any ulcer, plantar ulcer, ulcer at high-risk location), effectiveness of the intervention will be assessed using chi-square analysis. Outcome of ulcer recurrence over time will be assessed using log-rank testing and presented as Kaplan–Meier plots censored for death. For adherence to wearing custom-made footwear, Student’s *T*-test for independent samples will be done, provided the data is normally distributed. Cost and utility outcomes will be combined in the economic evaluation to calculate cost (savings) per QALY (gained) per participant (i.e., cost-utility). Incremental cost-utility ratios (ICUR) will be calculated as the ratio between costs and QALY differences between enhanced therapy and usual care. To account for sampling variability, non-parametric bootstrapping stratified for group and participating center category will be done with 5000 replications. Results will be displayed graphically by plotting the bootstrapped differences in costs and QALYs in a cost-utility plane, with the percentage of pairs in each quadrant calculated. Finally, cost-utility acceptability curves (CUAC) for willingness to pay values up to €100,000 will be graphically displayed, with the probability of enhanced therapy being cost-effective over usual care calculated for willingness-to-pay levels of €0,- and €50,000 per QALY gained and €0,- and €20,000 per extra participant without foot ulcer recurrence, respectively.

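### The intervals for the secondary cost and QALY differences are stratified on variables picked for association with the outcome: too narrow if resampling is also within arm, and no other reading of the clause helps

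*Protocol article*

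**What the plan says.** Under Statistical methods {20a}, Other study outcomes, the protocol article compares costs and QALYs between the arms by unadjusted two-sample t-tests. The test is to be reported "with 95% bias-corrected and accelerated confidence intervals around the mean difference to account for sampling variability". The clause at issue closes that sentence and says how the strata are found: the analysis is to be "stratified for a maximum of two variables that are univariately associated with the outcome". No covariate-adjusted estimate is named. There is no list of candidate variables, no restriction to variables measured before randomisation, and no statement on whether resampling is also done within arm.

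The section on primary study outcomes describes the other bootstrap, for cost-utility: "non-parametric bootstrapping stratified for group and participating center category will be done with 5000 replications". There, arm and centre are named as strata.

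General rules for testing: "All tests will assess group effects, will be two-sided", and they "use *P* < 0.05 as significance level".

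Sequence generation {16a} stratifies randomisation by participating centre and by time since healing of the last ulcer, with a gender-specific cut-off. Secondary objectives and Outcomes {12} list costs and QALYs as secondary outcomes.

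**The concern.** A BCa interval is a bootstrap interval, so the natural reading of the clause is stratified resampling. Stratified resampling holds the stratum counts fixed in every resample. That is correct for counts the design fixed. It is not correct for prognostic variables whose balance between arms was left to chance, when the estimate is the raw mean difference: part of that difference's real sampling variation is chance imbalance on those variables. Picking variables because they are associated with the outcome picks those for which the omitted part is largest.

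At stake is whether a reported cost or QALY interval that excludes zero reflects more than chance imbalance, and whether interval and t-test can give opposite answers on the same difference. The same two differences would also be bootstrapped under two sets of strata, so the reported intervals need not match the scatter shown in the cost-utility plane.

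**Working it through.** **Inputs from the protocol article.** 63 per arm ("this leads to a sample size of 63 participants per study group, or 126 participants in total"), 1:1 allocation, two-sided 5% level, group SD for QALYs 0.15 (Sample size {14}).

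**Input not in the document.** R², the share of outcome variance explained by the chosen variables. Assumed range: 0.1 to 0.4.

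**Reading 1: resampling within arm and within the chosen variables.**

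The raw difference has variance of about 2σ²/n. Resamples that fix the arm-by-stratum counts reproduce only the within-stratum part, 2σ²(1−R²)/n. Hence:

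- width ratio = √(1−R²)
- chance of excluding zero with no true difference = 2[1 − Φ(1.96·√(1−R²))]

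| R² | width ratio | false exclusion of zero |
|---|---|---|
| 0 | 1.000 | 5.0% (the nominal level) |
| 0.1 | 0.949 | 6.3% |
| 0.2 | 0.894 | 8.0% |
| 0.4 | 0.775 | 12.9% |

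On the QALY scale, the correct half-width is 1.96 × 0.15 × √(2/63) = 0.052. At R² = 0.4 the stated scheme would give 0.052 × 0.775 = 0.041.

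Simulation with no true difference used 63 per arm, binary baseline variables, up to two selected at univariate p < 0.05, BCa with 999 resamples, and 2,000 trials per scenario (Monte Carlo standard error about 0.5 points):

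| Scenario | Unstratified | Arm × chosen variables | Chosen variables only | t-test |
|---|---|---|---|---|
| Two candidates, R² 0.2, normal data | 4.5% | 8.8% | 4.8% | 4.1% |
| Two candidates, R² 0.4, normal data | 5.1% | 14.1% | 5.0% | 4.1% |
| Best two of ten, R² 0, normal data | 6.0% | 6.4% | 6.0% | 5.3% |
| Best two of ten, R² 0.1, normal data | 5.7% | 7.7% | 5.8% | 5.3% |
| Best two of ten, R² 0.2, normal data | 5.3% | 9.3% | 5.8% | 4.8% |
| Best two of ten, R² 0.2, skewed data | 7.1% | 11.8% | 7.6% | 5.0% |
| Best two of ten, R² 0.4, skewed data | 7.2% | 17.7% | 6.5% | 5.4% |
| Chosen variables are the randomisation strata, R² 0.2, normal data | 3.4% | 6.6% | 3.6% | 3.0% |

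A separate simulation with percentile intervals gave about 8%, 11% and 15% at R² 0.1, 0.2 and 0.4 for the arm-crossed scheme, against about 6% for arm-only resampling and 5% for the t-test. Formula and simulations together give about 6% to 15%; skewed data can go somewhat higher.

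**Reading 2: resampling within the chosen variables, arms together.** The simulated width is 0.99 to 1.00 of the unstratified width, and the error is essentially unchanged. The clause has no material effect.

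**Reading 3: the clause means an adjusted analysis.** No arithmetic applies. Covariates would be selected on outcome data, with nothing to keep out a variable measured after randomisation. Adjusting for a variable that treatment changes can remove part of the treatment effect.

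**The case against.** The strongest reply is that the sentence names only the chosen variables as strata. Where the authors want arm as a stratum they write it, as in the cost-utility bootstrap. On that literal reading the interval keeps roughly its nominal level. This stands: a reader might infer that the planned intervals are certainly too narrow, but the document does not settle it. Narrowing follows only if arm is crossed with the chosen variables.

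Three further points also stand. The stated test is the t-test, which keeps its level, so excess rejection arises only when significance is read from the interval. Time since healing is a randomisation stratum alongside centre and could well be one of the variables picked; most of the excess then disappears (6.6% at R² 0.2). And R² is assumed; near zero the effect is negligible.

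A reader might also infer a far larger error for costs, because nothing bars ulcer recurrence from being chosen. With 37% ulcers in both arms at €10,000 each, the between-stratum variance is 0.37 × 0.63 × 10,000² = 23.3 million. With an assumed SD of €1000 for other costs, R² = 23.3/24.3 = 0.96 and the formula gives about 69%; with an assumed €5000, R² = 0.48 and it gives about 16%. This is not a forecast. The protocol does not name ulcer recurrence as a stratum, the other-cost SDs are assumptions, and the first case implies a total cost SD of about √24.3 million = €4,930, against the planned €1000.

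The last reply is that such detail belongs in the analysis plan. That holds for candidate lists and software settings. But the protocol goes further and states a selection rule, and that rule is badly fixed.

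**Conclusion.** The point holds in conditional form. The clause either makes the interval too narrow (arm crossed with the chosen variables), does essentially nothing (chosen variables only), or opens the estimate to outcome-driven adjustment. No reading improves the analysis.

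Under the first reading, false exclusion of zero is about 6% to 15% for an assumed R² of 0.1 to 0.4, and less if the chosen variables are randomisation strata. This assumes that balance on the chosen variables was otherwise left to chance.

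The reach is limited to the secondary cost and QALY differences. Because costs and QALYs are the components of cost-utility, a reader might infer that the primary result is compromised. The documents do not support that: the primary bootstrap uses arm and centre and does not depend on the selection rule.

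**What to change.** Delete the clause on outcome-associated stratifying variables and bootstrap the cost and QALY differences within arm and participating centre, as already planned for cost-utility. One resampling scheme then serves both the intervals and the cost-utility plane.

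If prognostic variables are wanted, put them in the estimate: regress the outcome on arm plus covariates named in advance and measured before randomisation, preferably the randomisation strata (centre and time since healing), and bootstrap the adjusted difference. In either case, state that no post-randomisation variable, ulcer recurrence included, may be a stratum or covariate.

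The cost is one sentence and no new data. Intervals for the raw difference may be somewhat wider than under arm-crossed stratification.

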#### Secondary objectives

The secondary objectives are to assess the effects of an integrated personalized assistive devices approach in people with diabetes who are at high risk of ulceration on foot ulcer recurrence on the plantar surface and at high-risk locations; ulcer-free survival days; falls; wearing time of prescribed footwear; in-shoe peak plantar pressure; cumulative plantar tissue stress; footwear wear-and-tear; ulcer risk prediction score; treatment and footwear satisfaction; foot-related self-care; knowledge of foot care; capabilities, opportunities, and motivations to perform recommended footwear behavior (COM-b) score; quality of life; physical activity; costs; quality-adjusted life years; and cost-effectiveness. For participants who develop a foot ulcer, secondary outcomes further include time to ulceration, ulcer severity, time to healing, and referral time.

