### Outcomes {12}

There are three primary study outcomes in this study, which are:Foot ulcer recurrence during the 12-month follow-upAdherence to wearing custom-made footwearThe cost (savings) per quality-adjusted life year (QALY) gained (i.e., cost-utility)

These represent a clinical, patient-related, and health-economic perspective, respectively. Foot ulcer recurrence is defined as “a break of the skin of the foot that involves as a minimum the epidermis and part of the dermis, in a person who has a history of foot ulceration, irrespective of location and time since the previous foot ulcer” [15], is monitored during the entire study period, and is—on group level—calculated as the proportion of participants with one or more foot ulcers during the study period. Footwear adherence is defined as the percentage of steps taken in prescribed footwear, calculated by combining physical activity and wearing time measurements [44]. It is calculated over 1 week, at baseline and (for outcomes) at 6 and 12 months’ follow-up. Cost-utility is monitored during the entire study period, costs are summed throughout the 12-month period [45], and utility is scored with the EQ-5D-5L questionnaire every 3 months [46].

Secondary study outcomes are as follows: proportion of participants with one or more recurrent foot ulcers on the plantar side of the foot [15]; proportion of participants with one or more recurrent foot ulcers at the predefined personalized high-risk locations [15]; ulcer-free survival days [47]; falls [48]; wearing time of custom-made footwear [49]; in-shoe peak plantar pressure [47]; cumulative plantar tissue stress [44]; footwear wear-and-tear [50]; ulcer risk prediction score [29]; treatment and footwear satisfaction [51]; foot-related self-care [52]; knowledge of foot care [53]; capabilities, opportunities, and motivations (COM-b) score [54]; quality of life (in participants with [55, 56] or without [5] a recurrent foot ulcer during the trial); physical activity [57]; costs [45]; QALYs [46]; and cost-effectiveness [45]. In participants with an ulcer, other secondary outcomes are as follows: time to ulceration [58], ulcer severity [59–61], time to healing [58], and referral time [62]. Definitions for all secondary outcomes are as provided in the reference following each secondary outcome. All secondary outcomes are monitored during the entire study period using assessments and questionnaires during follow-up visits (see Fig. 2).

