### Sample size {14}

Based on an analysis of RCTs that have recurrent foot ulcers in people with diabetes as outcome, a risk reduction in participants with one or more recurrent foot ulcers up to 75% can be expected from a state-of-the-art multimodal treatment approach [63]. Using a more conservative estimate, we expect a risk reduction of 59% for the enhanced therapy group compared to usual care. This is based on previous studies that show that footwear and at-home foot temperature monitoring interventions combined can achieve such effect sizes [2, 15, 63]. With an expected ulcer recurrence in 37% of the participants in usual care [2, 20], this 59% risk reduction leads to a hypothesized 15% ulcer recurrence rate in the enhanced therapy group. With 15% ulcer recurrence in enhanced therapy and 37% in usual care, *α* = 0.05 (two-sided) and power = 80%, enrolment ratio of 1, power calculations show that 122 participants are required (61 per study group). We expect no dropout or missing data for the intention-to-treat analysis of the clinical outcome based on previous trial experience that clinical outcome can be obtained in each participant [20], which means that a total 122 participants are required for the primary clinical outcome.

For footwear adherence as the primary patient-related outcome measure, we expect 71% (sd 25%) adherence in usual care at 12 months based on findings from previous research [10, 12]. We expect an increase in footwear adherence in the enhanced therapy group to a level of 85% at 12 months, through the effect of indoor footwear provision [12] and structured education. With *α* = 0.05 (two-sided) and power = 80%, enrolment ratio of 1, power calculations show that 100 participants are required (50 per study group). Including a drop-out rate of 20%, this leads to a sample size of 120 participants in total for the primary patient-related outcome.

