##### Assessments during follow-up

Each participant will be followed for 12 months. If a participant has a foot ulcer at 12 months, they will be followed for another 6 months or until healing, whichever comes first. Follow-up will take place after 3, 6, 9, and 12 months (FU3, FU5, FU7, and Final visit (FV), respectively). Prior to each regular study visit, all participants will receive the EQ-5D-5L questionnaire and study specified versions of the iMTA iMCQ and iMTA iPCQ to gather volume data on medical costs, family costs, and productivity loss [45]. Additionally, at 6 and 12 months, all participants also complete the study questionnaire (see the section “Assessments at baseline visit”), and at 12 months also the SF-36. Participants in enhanced therapy will hand in their weekly diaries.

Custom-made footwear wearing time will be assessed during each 3-monthly visit by reading out the OrthoTimer sensor in the shoe. At 6 and 12 months, physical activity is assessed by wearing the activity monitor for 1 week. At 12 months, barefoot and in-shoe plantar pressure measurements will be repeated. Use of intramural healthcare resources during the study will be obtained at final visit from the participants’ medical status. If a participant has a foot ulcer at 12 months, visits will be scheduled at 15 and 18 months, or 2 weeks after healing (whichever comes first). During these visits, volume data on medical costs, family costs, and productivity loss will be gathered (iMTA) and the EQ-5D-5L will be completed. An overview of all measurements can be seen in Fig. 2.

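### Time to healing is right-censored but is assigned a t-test or Mann-Whitney test, and comparisons made only in ulcerated participants are not labelled as non-randomised

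*Protocol article*

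**What the plan says.** The Outcomes {12} section defines a group of secondary outcomes on a subset: "In participants with an ulcer, other secondary outcomes are as follows: time to ulceration", followed by ulcer severity, time to healing and referral time. The Secondary objectives section makes the same restriction: "For participants who develop a foot ulcer, secondary outcomes further include time to ulceration, ulcer severity, time to healing, and referral time".

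The Other study outcomes section first deals with costs, QALYs and cost-effectiveness. For all other parameters it refers the reader back to Outcomes {12} and says that "differences between enhanced therapy and usual care will be assessed via independent sample" t-tests if the data are normal and Mann-Whitney tests if not. Chi-square or Fisher tests apply "in case of nominal or ordinal data". It makes no exception for time to healing and gives no censoring rule.

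On follow-up, the Assessments during follow-up section says of a participant with an ulcer at 12 months that "they will be followed for another 6 months or until healing, whichever comes first". Participant timeline {13} gives the same ceiling of 18 months. The retention section {18b} foresees both withdrawal and death.

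The Primary study outcomes section already contains a time-to-event analysis: "Outcome of ulcer recurrence over time will be assessed using log-rank testing", with Kaplan-Meier plots censored for death. It states no restriction to participants who ulcerate.

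**The concern.** There are two separate problems.

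**Censoring.** An ulcer still open at last contact has a healing time known only to exceed the time observed. A t-test or Mann-Whitney test has no place for such a value. The longest healing times are the likeliest to be cut off, so omitting them or counting them as complete shortens the apparent healing time. The observation window also differs between ulcers: about 18 months for an ulcer at the start of follow-up and 6 months for one at month 12.

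**Conditioning on a treatment-affected event.** Time to healing, severity and referral time exist only for people who ulcerate, and the trial is designed on the expectation that treatment changes who they are. A comparison within that subset is not protected by randomisation. If the ulcers that treatment prevents tend to be the milder ones, those remaining under enhanced therapy will look worse even though treatment has harmed nobody.

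**Working it through.** **1. The plan's own figure.** The Sample size {14} section works from these rates: "With 15% ulcer recurrence in enhanced therapy and 37% in usual care". With two-sided alpha 0.05, 80% power, pooled variance and no continuity correction:

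n per arm = [1.960·√(2·0.26·0.74) + 0.842·√(0.37·0.63 + 0.15·0.85)]² / 0.22² = (1.216 + 0.505)² / 0.0484 ≈ 61.2, rounded up to 62.

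That is 124 in total, against the stated 122. At 61 per arm the power is 79.9%, so the figure is reproduced. The article gives no figure for time to healing.

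**2. Size of the ulcerated subset.** At 63 per arm (126 in total):
- enhanced therapy: 0.15 × 63 = 9.5
- usual care: 0.37 × 63 = 23.3
- both arms: about 33 of 126

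The standardised difference detectable with 80% power is (1.960 + 0.842)·√(1/9.45 + 1/23.31) = 1.08 SD. Only very large differences would be seen.

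**3. How much censoring to expect.** These are assumptions, since the article gives no healing times: onset uniform over 12 months, exponential healing with median m, and follow-up of open ulcers to month 18, with no earlier loss. Available follow-up is then uniform from 6 to 18 months. With λ = ln 2 / m:

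- share unhealed, s = (e^(−6λ) − e^(−18λ)) / (12λ)
- true mean = 1/λ
- mean if open ulcers are treated as complete = (1/λ)(1 − s)

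For m = 6: s = (0.500 − 0.125) / 1.386 = 0.27.

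| Median healing (months) | Unhealed at end | True mean | Mean, healed ulcers only | Mean, open ulcers treated as complete |
|---|---|---|---|---|
| 2 | 3% | 2.9 | 2.6 | 2.8 |
| 3 | 8% | 4.3 | 3.4 | 4.0 |
| 4 | 15% | 5.8 | 4.0 | 4.9 |
| 6 | 27% | 8.7 | 4.7 | 6.3 |

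Both shortcuts understate the mean, and more so as healing slows. If onset and healing were the same in both arms, the understatement would be equal too. If healing differs, the contrast shrinks. Medians of 3 and 6 months give a true ratio of means of 8.66/4.33 = 2.0, but 4.70/3.45 = 1.36 among healed ulcers.

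**4. What conditioning can do.** Assume that the prevented ulcers (22 of every 37 under usual care) are milder by d SD and that treatment has no other effect on severity. The spurious difference against enhanced therapy is d × 22/37. The last column is the simulated Mann-Whitney rejection rate at a nominal 5%, over 4,000 trials per row.

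| d (SD) | Spurious difference (SD) | Rejection rate |
|---|---|---|
| 0 | 0 | 4% |
| 0.25 | 0.15 | 7% |
| 0.5 | 0.30 | 10% |
| 1.0 | 0.59 | 25% |

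**5. Time to ulceration.** Under constant hazards the design rates give a hazard ratio of ln(0.85)/ln(0.63) = 0.35. A log-rank test in all randomised participants, with about 33 events, has about 85% power. A Mann-Whitney test among the ulcerated only has about 5%, because the conditional mean times are nearly equal (5.8 versus 5.5 months). It therefore matters that the text says which analysis applies.

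**The case against.** The strongest reply is that most of this is already covered. The general rule applies to outcomes not yet given a test, and the Primary study outcomes section gives ulcer recurrence over time a log-rank test. That section also assigns tests to secondary outcomes such as plantar ulcers, so its heading does not limit it. A reader might infer that time to ulceration is compared only among the ulcerated and without regard to censoring. The documents do not support that. What remains is that its definition in Outcomes {12} is restricted to the ulcerated and is not tied to the log-rank test.

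On severity, a reader might infer that the planned test is invalid. It is not. A grade is not censored, and chi-square on ordered categories is valid though less efficient. An ordered scale that places no ulcer below the grades would be a different outcome, not a repair of this one.

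On healing, it is fair to say that each ulcer can be followed for at least 6 months, that censoring is slight if healing is fast, and that the article nowhere says open ulcers will be dropped. Ranking them as longest, or using the multiple imputation in section {20c}, is possible. Neither fully repairs the analysis. Ranking an ulcer censored at 6 months above one that healed at 10 may be wrong. Predictive mean matching borrows observed healing times, and nothing stated keeps an imputed time longer than the time already spent unhealed.

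The restriction to ulcerated participants is stated openly, and measures in all randomised participants exist. That limits the harm, but the statistical section still treats these subset results as differences between treatments, without a caveat. Details may be left to an analysis plan that is not shown, but here the article itself assigns a test unsuited to the outcome.

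**Conclusion.** The point holds for time to healing: a right-censored outcome is assigned tests that cannot handle censoring. Its size is uncertain. The 3% to 27% unhealed rests on assumed onset and healing patterns, and death or withdrawal would add to it.

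For time to ulceration, the three sections on outcome definition, log-rank test and general rule only need to be brought into agreement. For severity and referral time, as for healing, the remaining point is that the comparison is not a randomised one. The possible distortion of 0.15 to 0.59 SD depends on an assumed gap in severity.

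All of these are secondary outcomes, in about 33 expected participants. A reader might infer a threat to the trial's main conclusions, but none of the three primary outcomes is affected.

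**What to change.** 1. Exempt time to healing from the general rule in Other study outcomes. Analyse it from ulcer onset by Kaplan-Meier and log-rank, with censoring at last contact.
2. State that the log-rank test in Primary study outcomes, in all randomised participants, is the between-arm analysis of time to ulceration, and align Outcomes {12} and Other study outcomes with it.
3. Label comparisons made only in ulcerated participants (time to healing, severity, referral time) as descriptive and non-randomised. A log-rank test handles the censoring of healing time but does not remove this selection.
4. Use ulcer-free survival days, already listed in Outcomes {12}, in all randomised participants for between-arm inference.

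The cost is a small amount of analysis-plan rewording, with no new data and no change in sample size.
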